### Dissemination

This protocol will be published and disseminated as a thesis on *pratishyaya*. The study protocol provides a detailed overview of the study design, methodology, data collection procedures, data analysis plan, and ethical considerations. By disseminating this protocol, we hope to advance knowledge in the field and facilitate future research.

## Results

As of November 2024, we completed the enrollment of 70 patients, with 35 patients in each group. A total of 4 patients voluntarily withdrew from the trial. Data analysis of 66 patients will be completed by February 2025, and we expect the results to be published in March 2025.

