**Methods:**

A total of 70 participants fulfilling the inclusion criteria were selected and distributed into 2 groups of 35 each. The intervention group received *dhoopana* and the control group received polyherbal steam inhalation, both twice daily for 7 days. The primary outcome measure was the change in Total Nasal Symptom Score and a modified cold spatula test. At the same time, the association between *prakriti* (body constitution) and the prevalence of *pratishyaya* in children was analyzed as a secondary outcome. Assessments were performed on days 3, 5, and 7, with a follow-up time of 28 days. Appropriate descriptive and inferential statistics will be used for data analysis.

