### Trial Design

This will be a randomized, reference, controlled, open-label equivalence clinical study. A total of 70 patients have been recruited for the study.

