## Methods

### Recruitment

The patients were selected from the outpatient and inpatient departments of the Department of Kaumarabhritya (Ayurvedic pediatrics) of Mahatma Gandhi Ayurveda College, Hospital & Research Centre and from the surrounding region. After initial screening, the patients were randomized using computer-generated random numbers into 2 groups; the control group (polyherbal steam inhalation) and the intervention group (polyherbal nasal fumigation). All baseline parameters were recorded at the start of the study. Both groups underwent treatment for 7 days. All the parameters were recorded on the third, fifth, and seventh days, with a follow-up of 28 days after the treatment period. Patients were advised to drink warm water and stay away from cold and sour items. Patients were given regular counseling and reminders through calls or messages to follow the rules and regulations of the trial.

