### Withdrawal Criteria and Stoppage

No adverse effects of the trial drug were noted during the treatment period. Thus, no cases were excluded from the study. A total of 4 patients, including 2 patients in each group, voluntarily stopped taking treatment during the trial and were counted as withdrawn.

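### The only analysis set the article names is 66 children, the 70 randomised less four who stopped treatment; an as-randomised analysis of all 70 should stand beside it

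*Protocol article*

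**What the plan says.** Trial Design states the type of study: "This will be a randomized, reference, controlled, open-label equivalence clinical study". Under Recruitment, "the patients were randomized using computer-generated random numbers into 2 groups", and baseline values were taken at the start. The Abstract gives the number: "A total of 70 participants fulfilling the inclusion criteria were selected and distributed into 2 groups of 35 each".

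Withdrawal Criteria and Stoppage reports: "A total of 4 patients, including 2 patients in each group, voluntarily stopped taking treatment during the trial and were counted as withdrawn". Just before this, having noted no adverse effects, the same section says "Thus, no cases were excluded from the study".

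Results confirms that "we completed the enrollment of 70 patients, with 35 patients in each group". It then describes the four as having left the trial of their own accord and continues: "Data analysis of 66 patients will be completed by February 2025". Data Analysis lists tests (Student t, Wilcoxon, Mann-Whitney) and does not name an analysis set.

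**The concern.** Randomisation protects the comparison only while children are analysed in the groups to which they were allocated. Here the named set leaves out children because of something that happened after allocation. Parents gave the treatment at home and knew which one it was, and TNSS is subjective. A decision to stop could follow from poor relief, from dislike of the procedure or from early recovery. Each of these bears on the outcome, and they need not operate alike in the two arms. The article gives no reasons for stopping, and two per arm shows balance in number only.

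The stake is the equivalence claim. If the four differ from the 66 in opposite directions in the two arms, a set without them can look more alike than the randomised groups were. The reverse risk is also real: in an equivalence trial an as-randomised analysis can pull the arms together. Neither set is sufficient alone.

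A second difficulty is that the article gives two accounts of the same children. Stopping treatment leaves later assessments possible; leaving the trial usually ends them. Which account holds decides what an analysis of all 70 can use.

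**Working it through.** **Inputs.** Randomised: 35 + 35 = 70 (Abstract, Results). Withdrawn: 2 + 2 = 4 (Withdrawal Criteria and Stoppage). To be analysed: 66 (Results). Sample size: α = .05, β = .2, proportions 0.60 and 0.90, minimum 32 per arm, 10% withdrawal allowance (Sample Size).

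**1. The plan's own figures.**
- 70 − 4 = 66, that is 35 − 2 = 33 per arm. The figure reproduces exactly, so the 66 are the randomised children less those counted as withdrawn.
- The usual two-sided formula for two proportions with pooled variance, n = [1.96·√(2·0.75·0.25) + 0.84·√(0.60·0.40 + 0.90·0.10)]² / 0.30², gives 31.5, hence 32 per arm, as stated.

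**2. Share left out.** 2/35 = 5.7% per arm and 4/70 = 5.7% overall, below the planned 10%. The 66 still exceed the stated minimum of 64.

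**3. Is this a loss of power?** No. For 0.60 versus 0.90, the only contrast the article quantifies, power is 81.9% at 33 per arm and 84.1% at 35 per arm. The issue is who is analysed.

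**4. How far could the four move a responder difference?** Let a and b of 33 respond in the two arms. The difference among the 66 is (b − a)/33. On all 70 it ranges from (b − a − 2)/35 to (b − a + 2)/35, according to the four outcomes.
- Equal responders (a = b): difference 0 among the 66; range −2/35 to +2/35, or −5.7 to +5.7 points, whatever the common rate.
- 20 versus 30 responders: 10/33 = 30.3 points among the 66; range 8/35 = 22.9 to 12/35 = 34.3 points.

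The ends of each range need both withdrawals in one arm to respond and both in the other to fail.

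**5. On a mean score.** The difference on all 70 is (33/35) × the difference among the 66 + (2/35) × the difference among the withdrawn. If the 66 show no difference, each point by which the withdrawn children of the two arms differ on average moves the result by 2/35 = 0.057 points. No data are given from which to put a value on this.

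**6. Counting all four as unimproved.** The difference becomes (b − a)/35, which is 33/35 = 0.94 of the difference among the 66. With 20 versus 30 responders, 30.3 points becomes 10/35 = 28.6. A zero difference stays zero. With two withdrawals per arm this rule can only shrink a difference, so it cannot test an equivalence claim.

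**7. The statements side by side.** One section says the four "voluntarily stopped taking treatment during the trial and were counted as withdrawn"; Results says they left the trial. The sentence that no cases were excluded follows from the absence of adverse effects, so it need not contradict the 66, but it reads awkwardly beside it. Nothing says whether the four had assessments on day 3, 5 or 7 before stopping, or any afterwards.

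**The case against.** The strongest reply is that the Results sentence reports progress and does not define an analysis population. An article condenses a fuller plan, and a second analysis set, missing-data rules and sensitivity analyses are commonly kept for that plan. This stands in part: a reader might infer that the article rules out an as-randomised analysis, and it does not say so. What remains is that it names a number, 66, and no other.

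Second, a reader might infer that outcome data on the four exist and are being thrown away. The documents do not support that. Results says the four left the trial, and the 66 may simply be the children with outcomes. This objection stands, and it is why the two descriptions must be reconciled.

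Third, a per-protocol set is legitimate in an equivalence trial, since an as-randomised analysis can itself favour similarity. This stands too, and is the reason to keep the 66 as a companion set.

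Fourth, the loss is small, equal in number and anticipated, and the section on withdrawals reports no adverse effects, so nothing points to poor tolerance. This limits the weight of the point without removing it, because the reasons for stopping are not given.

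**Conclusion.** The point holds in a limited form. The one analysis set the article names is the randomised children less four who stopped treatment, and in an open-label equivalence trial with a subjective primary outcome such a set should not carry the conclusion alone. The four are 5.7% of each arm.

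The ±5.7-point range assumes a responder endpoint, as in the sample-size section, equal rates among the 66, and the most extreme split of the four. The primary outcomes are change in TNSS and the modified cold spatula test, and the effect on those scales cannot be estimated from the article.

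Two stronger readings should be avoided. One is that 5.7 points uses up some given share of the equivalence margin: the article states no margin, so no such share can be calculated. The other is that leaving out the four has biased the result: no reasons or outcomes for them are reported, so bias is possible but not shown.

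**What to change.** - Reconcile Withdrawal Criteria and Stoppage with Results: say whether the four stopped treatment only or also left follow-up, when, for what reasons if known, and which assessments they have.
- Analyse all 70 children by allocated group, using every TNSS and fogging value recorded on days 3, 5 and 7 and at follow-up, with the handling of missing values stated.
- Report the 66 alongside, labelled as the per-protocol set, and claim equivalence only if both sets support it.
- As a sensitivity analysis, give the best/worst-case range that sets the two withdrawals in each arm in opposite directions, against each arm in turn. Do not rely on counting all four as unimproved.

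The cost is a few extra analysis runs and possibly a slightly less favourable interval. No further recruitment is needed. If the four have no outcome data after baseline, the analysis of all 70 will rest on the stated missing-data assumption and the best/worst-case range, and the report should say so.

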## Discussion

*Dhoopana* is mentioned in the Ayurveda classics for the management of acute rhinitis, and we anticipate that it will be found to be equally effective as polyherbal steam inhalation in the management of acute rhinitis in children. Steam inhalation of the herbs that were chosen for this study has been found to be effective in the management of upper respiratory tract infections. Thus, fumes of the same ignited herbs (ie, *tulsi*, *vasa*, *nirgundi*, and *nilgiri*) should work just as well in the management of rhinitis. The disease *pratishyaya* is very common in the pediatric population, but no standardized Ayurvedic therapy is available that can be given locally in the nostrils in its acute stage. Locally given medicines are fast and effective compared to oral medication. Another classical procedure known as *nasya* (nasal instillation of oil) is recommended for rhinitis, and as per previous research, it is effective in the management of chronic and recurrent rhinitis, but as per the Ayurveda classics, it cannot be used in acute rhinitis. The herbs chosen for this study are hot and pungent in nature and can reach the minute *srotasa* (channels of the nostrils); thus, they promise to be beneficial in acute rhinitis. Polyherbal *dhoopana* is safe and easy to administer, and if it is found to be effective, it may be a better alternative to steam inhalation. Thus, it can be used in general pediatric practice for patients with acute rhinitis. A positive outcome of the study will facilitate further studies in a large population with standardization of the procedure for *dhoopana*. In this study, a polyherbal wick was prepared manually, and it takes some time to ignite the herbal powder. In the future, this can be improved by using a pocket-friendly herbal nasal fumigator that ignites the herbs in few seconds without any manual practice. This could be patented and copyrighted later and publicized for the benefit of the population.

## Appendix

Multimedia Appendix 1 Images of intervention.

## Abbreviations

CONSORT: Consolidated Standards of Reporting Trials
TNSS: Total Nasal Symptom Score
